### Statistical analyses

Per-protocol analysis will be conducted for primary endpoints using data from completers at 3 months. Intention-to-treat analysis will be conducted using the imputed full analysis set as sensitivity analysis. Missing data from those who provided data other than baseline will be imputed using the last observation carried forward (LOCF) method for symptom and depression scores. SPSS Statistics (version 26, IBM Corp., Armonk, NY, USA), SAS (version 9.4, SAS Inc., Cary, NC, USA), R (version 4.0.2, Institute for Statistics and Mathematics, Vienna, Austria, www.R-project.org), and Mplus (version 8.4, MPLUS, Los Angeles, CA, USA) software will be used for data analysis.

Primary hypothesis: Advanced cancer patients who receive “Enhanced Supportive Care” (symptom management + coping enhancement counseling) will demonstrate fewer symptoms and better coping and QoL at 3 months (T5) compared to the control group of advanced cancer patients who receive usual care with symptom monitoring only.

Secondary hypothesis: Advanced cancer patients who receive “Enhanced Supportive Care” (symptom management + coping enhancement counseling) will demonstrate fewer symptoms and better coping and QoL at 6 months (T6), less depression, higher self-efficacy for coping with cancer at 3 months (T5) and 6 months (T6). Changes in symptoms and depression from baseline (T1) to 3 months (T5) will be different between the intervention and control groups. The intervention group will demonstrate longer survival at 6 months (T6) and 12 months (T7) than control group. Family caregivers of advanced cancer patients who receive “Enhanced Supportive Care” will demonstrate less depression than family caregivers of patients who were assigned to the control group at 3 months (T5) and 6 months (T6).

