### Study procedures

The intervention group will receive the “Enhanced Supportive Care” consisting of 1) symptom management web-based symptom management system using iPad at each clinic visit (20 min) and 2) coping enhancement counseling (30 min). The “Enhanced Supportive Care” will be provided by trained nurses for 5 times over 3 months. Control group participants will monitor symptoms using web-based symptom management system using iPad at each clinic visits for 5 times and their symptom report will be delivered to oncologist via EMR, whereas neither evidence based symptom management education (using iPad and booklet) nor coping enhancement counseling by research nurses will be provided.

Participants could withdraw from the study upon request, and those who transfer to different hospitals, whose condition is deteriorated for study participation will be withdrawn from the study. Upon patients’ withdrawal, caregiver will withdraw as well.

Double data entry will ensure the integrity of the data. Collected information will be coded and stored for security, and the data will be monitored every 6 months.

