**Fig. 3 Fig3:**
[figure not shown]
Schedule of enrollment, interventions, and assessments

Edmonton Symptom Assessment Scale (ESAS) [44] + 4 core symptoms recommended to be evaluated in clinical trials (constipation, diarrhea, peripheral neuropathy) [45] as well as vomiting (expert opinion) (a total of 15 items (14 symptoms and 1 well-being item)) will measure symptom. Hospital Anxiety and Depression Scale (HADS) [46] will be used to measure depression of patients and family caregivers. Self-efficacy for coping with cancer will be evaluated using the Cancer Behavior Inventory (CBI) 3.0 Korean version [47]. Brief COPE [48] and EORTC QLQ C-30 [49] will be used to evaluate coping and QoL of patients. Data will be collected at baseline (before the start of first-line palliative chemotherapy), at 3 months, at 6 months, and at 12 months. Symptoms and depression during chemotherapy cycles (1^st^ to 4^th^ CTx) will be monitored (Fig. 3).

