### Endpoints

The primary endpoints are symptoms, coping, and QoL at 3 months. Secondary endpoints are symptoms, coping, and QoL at 6 months, depression and self-efficacy for coping with cancer at 3 and 6 months, symptom and depression change from baseline to 3 months, survival at 6 and 12 months among patients, and depression among caregivers at 3 and 6 months. Any withdrawal from adverse events related to the intervention will be recorded and reported.

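### The stated intention-to-treat check brings in no patient missing at 3 months for coping or quality of life, and uses last observation carried forward for symptoms

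*Protocol article*

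**What the plan says.** Under Endpoints: "The primary endpoints are symptoms, coping, and QoL at 3 months". Under Statistical analyses, the main analysis of these is restricted: "Per-protocol analysis will be conducted for primary endpoints using data from completers at 3 months". The check on it follows: "Intention-to-treat analysis will be conducted using the imputed full analysis set as sensitivity analysis". The next sentence gives the one imputation rule in the article, whose operative words are: "those who provided data other than baseline will be imputed using the last observation carried forward (LOCF) method for symptom and depression scores".

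The Outcome measures section gives the timing. Brief COPE and the EORTC QLQ-C30 "will be used to evaluate coping and QoL of patients". For the instruments as a whole, "Data will be collected at baseline (before the start of first-line palliative chemotherapy), at 3 months, at 6 months, and at 12 months". The extra assessments around treatment cycles are described for two constructs only: "Symptoms and depression during chemotherapy cycles" are to be monitored.

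The Primary endpoints paragraph of the analysis section specifies an independent t-test at 3 months. The Secondary endpoints paragraph adds a linear mixed model for change to 3 months in symptoms and patients' depression. Under Study procedures, "those who transfer to different hospitals, whose condition is deteriorated for study participation will be withdrawn from the study".

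**The concern.** A completer analysis compares the patients who remain, not the groups as randomised. Here, deterioration is itself a stated ground for withdrawal, so those missing at 3 months (T5) are unlikely to resemble those who stay. The intention-to-treat analysis is the plan's stated protection against this, and it can only protect if it brings in the patients whom the completer analysis drops.

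For coping and quality of life the stated rule brings in none of them. For symptoms it brings in some, but by a single imputation that holds a patient who left while worsening at an earlier score and treats the filled-in value as observed. The trial could therefore report that its primary results were robust to missing data when, for two of three primary endpoints, this had not been tested.

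**Working it through.** **1. Who can enter the T5 t-test under the stated rule**

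| Endpoint | Named in the imputation rule? | Assessed between T1 and T5, per the text? | Patient missing at T5 enters? |
|---|---|---|---|
| Symptoms | Yes | Yes, during chemotherapy cycles | Only with some post-baseline data |
| Coping | No | No | No |
| Quality of life | No | No | No |

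Reading the rule more widely does not help. A patient lost before T5 has only a baseline coping or quality-of-life score, and the rule is confined to patients with data beyond baseline. A patient who misses T5 but returns at 6 months (T6) has a later value, which carrying forward cannot use. The t-test drops anyone without a T5 value.

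**2. How many patients**

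Inputs from Sample size determination: 360 patients, 20% drop-out. Assumption: all drop-out occurs by T5.

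- Missing at T5: 0.20 × 360 = 72
- With T5 data: 360 − 72 = 288

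Power is not the issue. The plan's t-test total of 192 reproduces at a standardised effect of 0.50 with power 0.93 per endpoint (95.4, so 96 per arm; 2 × 96 = 192; joint power 0.93³ = 0.804). With 288 patients, power at 0.50 is 0.988. The issue is bias.

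**3. What the check cannot see for coping and quality of life**

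Let m be the share missing, the same in each arm, and g the difference between the treatment effect in completers and in the missing. The completer effect then differs from the all-randomised effect by m × g. The values of g, and of m other than 20%, are assumed.

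| m | g = 0.25 SD | g = 0.50 SD |
|---|---|---|
| 10% | 0.025 | 0.05 |
| 20% | 0.05 | 0.10 |
| 30% | 0.075 | 0.15 |

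A check that leaves out the same missing patients cannot detect a shift of this kind.

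**4. Size of the carried-forward bias for symptoms**

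This was simulated under no treatment effect: five visits, autocorrelation 0.7, 180 patients per arm, drop-out driven by the last score. All of these settings except the arm size are assumptions. Ranges are across two sets of runs.

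| Drop-out by arm | Worsening | Absolute bias (SD) |
|---|---|---|
| 20% / 20% | any tried | about 0 |
| 25% / 15% | 1 SD | 0.023 to 0.024 |
| 30% / 10% | 1 SD | 0.052 to 0.055 (rejection rate 0.083 at nominal 0.05) |

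The direction of the bias changed with the assumed disease course. In these runs about 2% to 10% per arm had baseline data only. That share is simulation output, not a figure for this trial.

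**The case against.** The strongest reply is that the article promises an imputed analysis set without saying that coping and quality of life go unimputed, and a separate analysis plan may supply their method. The schedule figure is also not available, so the visit pattern rests on the text. This would settle the matter if the article were silent on imputation. It is not: it fixes a method, the scores it covers and the patients it covers, and that rule cannot deliver the promised check for two primary endpoints.

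Several stronger readings are tempting, and the documents do not support them:

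- **That the intention-to-treat analysis merely repeats the completer analysis.** This depends on what per-protocol means. If it also requires finishing the five sessions, intention-to-treat would add non-adherent patients who have T5 data. It would still add none who are missing at T5.
- **That 72 patients will be lost.** The 20% is tied to longitudinal follow-up, which runs to 12 months, so 72 by T5 is an upper figure under the plan.
- **That symptoms rest on carrying forward alone.** The secondary mixed model can use partial data from patients who drop out and is a real partial safeguard for symptoms and depression. It does not cover coping or quality of life.
- **That baseline-only patients are formally excluded, or that scores are deliberately carried past death.** The rule says whose data are imputed and does not define the full set. Baseline-only patients simply have no value to test. On death it is silent.
- **That carrying forward seriously distorts the trial's conclusion.** The worst simulated bias, 0.055 SD, is 0.055 / 0.50 = 11% of the effect planned for quality of life. It arises only with an assumed 30% / 10% drop-out gap and affects a sensitivity analysis.

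It is also true that patients withdrawn before T5 will often lack T6 as well. A mixed model for coping and quality of life would then use only their baseline, so the model alone is not a full answer.

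**Conclusion.** The concern holds in this limited form. As written, the intention-to-treat check adds no patient missing at T5 for coping or quality of life, and for symptoms it adds only those with post-baseline data, by a method poorly suited to withdrawal for deterioration. The gap for the two unimputed endpoints carries the point, and the symptom bias is secondary.

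Up to 72 of 360 patients could be outside both analyses, if all planned drop-out falls by T5. The reading takes the assessment schedule from the text and the imputation rule at face value. This should be fixed. It weakens the protection around the primary result but does not by itself show that result to be wrong.

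**What to change.** - **Intention-to-treat analysis:** replace last observation carried forward with a likelihood-based mixed model on all randomised patients. Put baseline among the responses, so that baseline-only patients contribute, and take the T5 contrast between arms as the estimate.
- **Scope:** extend the model already planned for symptoms and depression to coping and quality of life, using T1, T5 and T6.
- **Sensitivity:** add multiple imputation with a delta adjustment over a range stated in advance.
- **Deaths:** do not impute values after death, and report deaths by arm beside each result. The mixed model itself implicitly extends the course of patients who die, so its estimate should be read with those counts.
- **Completer t-test:** it can stay as a supporting analysis. State whether completer means having T5 data or also finishing the sessions.

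The cost is revised analysis wording and modest programming in SAS or R, both already listed. The mixed model relies on data being missing at random, which is doubtful when deterioration leads to withdrawal. The delta analysis is there to probe that assumption.

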#### Demographic and clinical characteristics

Frequency and percent, mean and standard deviation (or median), minimum and maximum, and interquartile rangeStandardized difference for homogeneity for baseline characteristics between intervention and control groups

#### Primary endpoints

Independent t-test to evaluate intervention effect for symptoms, coping and QoL at 3 months

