### Randomization and blinding

The random allocation sequence was developed by the principal investigator (PI) before initiating patient enrollment. Research nurses will enroll and allocate patients according to the predefined sequence. Stratified permuted block randomization will be used to assign participants in a 1:1 ratio to the intervention or control group. Strata include the type of cancer (lung, breast, colorectal, gastric, liver/biliary/pancreas, or other cancers), age and sex of cancer patients. The minimization method will be applied after enrolling 60% of the participants in each cancer group to balance group allocation. Blinding is not considered applicable based on the type of intervention provided.

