### Sample size determination

Advanced cancer patients (*n*=360) and their family caregivers (*n*=360) will participate in the study. Sample size was estimated based on two-sided tests with α=.05, power=.80 (=.93 x .93 x .93) considering three primary endpoints [50], and medium effect size (beta >.30) for supportive care interventions for symptoms [51], coping (.50~.55) [46], and QoL (.50) [52]. The estimated sample size for t-tests was 192, that for correlation analysis was 126, and that for multiple regression with 10 control variables was 160.

Considering structural equation modeling to analyze relationships among the studied variables, a sample size of > 300 is recommended [53]. Considering longitudinal data collection and a dropout rate of 20%, a total of 360 advanced cancer patients and 360 family caregivers will be enrolled in the study.

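### Primary endpoints and most secondary endpoints are tested with an unadjusted t-test, which leaves baseline scores and randomisation factors unused and costs precision for smaller effects

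*Protocol article*

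**What the plan says.** Under Primary endpoints, the protocol article specifies an "Independent t-test to evaluate intervention effect for symptoms, coping and QoL at 3 months". Under Secondary endpoints it names the same test for:

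- symptoms, coping and QoL at 6 months;
- patient depression and self-efficacy at 3 and 6 months;
- caregiver depression at 3 and 6 months.

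No covariate is attached to any of these tests. The other treatment-effect analyses are a linear mixed model for change in symptoms and patient depression up to 3 months, and a log-rank test for survival. Multiple regression and Cox regression are listed only as ways to find contributing factors.

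Under Randomization and blinding, "Stratified permuted block randomization will be used to assign participants in a 1:1 ratio to the intervention or control group". The section continues: "Strata include the type of cancer (lung, breast, colorectal, gastric, liver/biliary/pancreas, or other cancers), age and sex of cancer patients". Minimisation takes over once 60% of each cancer group is enrolled. The Outcome measures section places the questionnaires at baseline as well as at follow-up, and it assigns the HADS to patients and caregivers alike.

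**The concern.** The trial spends effort balancing the arms on three factors and measures each outcome scale before treatment. Its main test then uses none of this. Variance that the baseline score or the strata could explain stays in the error term, so confidence intervals are wider than they need be. Where the strata predict outcome, the t-test's standard error also still counts between-stratum variation that the allocation has already balanced, and the test rejects less often than its nominal level.

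What is at stake is precision, and chiefly power for effects below the 0.50 on which the t-test sample size rests. The plan aims for 93% power on each endpoint, so the endpoint with the smallest effect limits the joint power.

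**Working it through.** **Inputs from Sample size determination**

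- Significance level: "Sample size was estimated based on two-sided tests with α=.05".
- Power: "power=.80 (=.93 x .93 x .93) considering three primary endpoints", that is 0.93 per endpoint (0.93³ = 0.804).
- Effects: "medium effect size (beta >.30) for supportive care interventions for symptoms [51], coping (.50~.55) [46], and QoL (.50) [52".
- Stated result: "The estimated sample size for t-tests was 192".
- Enrolment: "Considering longitudinal data collection and a dropout rate of 20%, a total of 360 advanced cancer patients", so 360 × 0.80 = 288 completers, or 144 per arm.

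**Assumed inputs (not in the document)**

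- Baseline-to-follow-up correlation ρ: 0.3 to 0.7.
- Share of outcome variance explained by the strata, R²: 5% to 20%.
- The symptom figure of 0.30, labelled beta in the plan, is read as a standardised mean difference d.

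**Step 1: reproduce the plan's figure.** With d = 0.50, two-sided α = 0.05 and power 0.93, the normal approximation gives 2 × (1.960 + 1.476)² / 0.50² = 94.4. That rounds up to 95 per arm, or 190 in total. The exact noncentral-t solution is 95.4, which rounds up to 96 per arm, or 192. The stated 192 is therefore an unadjusted t-test calculation that takes no credit for baseline adjustment.

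**Step 2: unadjusted test with 144 per arm.** The standard error in SD units is √(2/144) = 0.1179.

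- Power at d = 0.50: Φ(0.50/0.1179 − 1.960) = 98.9%.
- Power at d = 0.30: Φ(0.30/0.1179 − 1.960) = 72.1%.
- Difference detectable with 93% power: (1.960 + 1.476) × 0.1179 = 0.405 SD.

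**Step 3: adjust for the baseline score.** ANCOVA multiplies the residual variance by 1 − ρ², so the standard error becomes 0.1179 × √(1 − ρ²). Relative efficiency is 1/(1 − ρ²).

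| ρ (assumed) | Relative efficiency | Total N for 93% power at d = 0.50 (normal approximation) | Power at d = 0.30, 144 per arm | Power at d = 0.50, 144 per arm | Detectable with 93% power (SD) |
|---|---|---|---|---|---|
| none (t-test) | 1.00 | 190 | 72.1% | 98.9% | 0.405 |
| 0.3 | 1.10 | 172 | 76.1% | 99.4% | 0.386 |
| 0.4 | 1.19 | 160 | 79.3% | 99.6% | 0.371 |
| 0.5 | 1.33 | 142 | 83.6% | 99.8% | 0.351 |
| 0.6 | 1.56 | 122 | 88.9% | >99.9% | 0.324 |
| 0.7 | 1.96 | 98 | 94.6% | >99.9% | 0.289 |

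**Step 4: ignore balanced strata.** If allocation is balanced on factors that explain a share R² of the variance, the true variance of the difference is (1 − R²) times what the t-test uses. The actual size is 2 × [1 − Φ(1.960/√(1 − R²))]:

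- R² = 5%: 0.044
- R² = 10%: 0.039
- R² = 20%: 0.028

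All are below 0.05. These values suppose that the balance achieved at allocation persists among the patients analysed.

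**The case against.** The strongest reply is that nothing here is an error. The t-test is unbiased under randomisation, it matches the method used to size the trial, and ignoring the strata lowers the false-positive rate. At the effects planned for coping and QoL (0.50 or more), 288 completers already give about 99% power, so adjustment buys almost nothing there. All of this stands.

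It is also true that neither ρ nor R² is in the document. Chemotherapy starts between baseline and 3 months, so a correlation as low as 0.3 is plausible. The efficiency gain is then only 10%. Because the primary analysis uses 3-month completers, dropout may disturb the balance on the strata and weaken the conservatism in Step 4.

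A reader might go further and infer three things that the document does not support:

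- **That the estimate is biased by chance imbalance.** Stratification and minimisation limit imbalance on the three factors. Chance imbalance in baseline scores is already allowed for in the t-test's standard error. Restriction to completers is a separate matter, which ANCOVA would not cure.
- **That the t-test and the mixed model for symptoms conflict.** The Endpoints section declares two endpoints, the 3-month level (primary) and change to 3 months (secondary), so it is clear which governs.
- **That the multiple regression already supplies the adjusted analysis.** A regression with 10 control variables is sized, but the regressions are listed only to identify contributing factors.

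What survives the reply is narrower: the document names a specific, less efficient test when better information is at hand, and the cost falls on smaller effects.

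**Conclusion.** The point holds as a recommendation on efficiency. It does not question the validity of the trial. At d = 0.50 the practical loss is negligible (98.9% against at least 99.4% power). At d = 0.30 it can matter: the unadjusted test has 72% power, well short of the 93% sought per endpoint, and adjustment raises this to 76% to 95%. The difference detectable with 93% power falls from 0.405 SD to between 0.386 and 0.289 SD.

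These ranges rest on an assumed correlation of 0.3 to 0.7 and on 20% dropout. Their relevance to symptoms rests on reading the figure labelled beta as a standardised difference. The conservatism (size 0.044 to 0.028) rests on the strata explaining 5% to 20% of the variance. That the plan uses an unadjusted test is certain; how much this costs is not.

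**What to change.** Replace the patient t-tests at 3 and 6 months by ANCOVA, or by the equivalent time-point contrast from a mixed model. Adjust for the same scale's baseline score, cancer type, age and sex. For caregiver depression, adjust for the caregiver's own baseline HADS score; the randomisation factors describe the patient, and the document gives no reason to expect them to predict caregiver depression. Report the unadjusted difference as supportive.

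No new data, visits or patients are needed. With age entered linearly, the patient model uses eight covariate parameters (1 for baseline, 5 for six cancer types, 1 for age, 1 for sex), which is slight against 288 completers. The change does reach the protocol, however, because the protocol itself names the t-test. Allocation is open and recruitment began in March 2021, so the change must be dated and made before any comparison by arm. If such a comparison has already been made, the adjusted analysis should be labelled as added afterwards.

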#### Secondary endpoints

Independent t-test to evaluate intervention effect for patients’ symptoms, coping and QoL at 6 months, patients’ depression and self-efficacy for coping with cancer at 3 and 6 months, and caregivers’ depression at 3 and 6 monthsLinear mixed model to evaluate intervention effect for change in symptoms and patients’ depression from baseline to 3 monthsPearson correlation and multiple regression analysis to identify factors contributing to symptoms, depression, coping, self-efficacy for coping with cancer and QoLKaplan‒Meier curve and log-rank test to evaluate intervention effect on survival at 6 and 12 monthsCox proportional hazard regression to identify factors contributing to survivalPearson correlation analysis, mediation and moderation analysis, and structural equation modeling to understand relationships among symptoms, depression, coping, self-efficacy for coping with cancer, and QoL

